**Fig. 2 fig2:**
[figure not shown]
The assigned tasks for each of the study groups.

### Incentives

3.7

Since this study is demanding and expects a high amount of commitment, we appreciate participants’ collaboration by allowing them to keep their MUSE headband at the end of the study after completion of the data collection. The participants who withdraw before completion are also allowed to keep their device.

### Blinding

3.8

Due to the nature of this RCT design, it is not possible for participants to be blinded to their group assignment. However, the subjects in all three groups will be coded and de-identified after initial meeting for the whole duration of data collection and data analysis procedure. They are requested to keep their contact by mentioning their given codes and fill out the questionnaires by submitting the USASK coded emails instead of their personal emails.

### Participants

3.9

According to A priori G*power software calculation for this study considering both between-subject and within-subject effects, a sample size of 66 is expected to detect significance level of 0.05 with 95 % power through our planned statistical analysis test, i.e., Repeated Measures ANOVA. We aim to look at the effect of time by comparing the baseline with mid-/post intervention reports of the participants for each of the six measurements independently; moreover, we will compare the interaction of time*groups separately for each of our six scales. We will initially allocate 180 participants; yet with reference to the previous studies [22], we could expect up to 50 % of attrition. After applying inclusion and exclusion criteria, participants will be selected for either the meditation, the control, or the waitlisted group. We speculate a higher number of attritions in the meditation and control groups regarding the complexity of the given tasks as compared to the waitlisted group. Fig. 3 provides a flowchart for the number of expected participants at each stage of the study.

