## Hypotheses

2

The main goal of the presented RCT protocol is to evaluate how 8 weeks of neurofeedback mindfulness using a wearable EEG headband could moderate headache experience (including frequency and intensity), headache management self-efficacy, psychiatric symptoms (i.e., anxiety and depression) and dependence on analgesics for adults with chronic migraine who are also identified as naïve meditators. The specific measures are described in more detail below. The following hypotheses are tested in this RCT.1.After completing the intervention, neurofeedback mindfulness will improve headache experience across time via:a.Decreased migraine disabilityb.Decreased migraine intensityc.Increased headache management self-efficacya.Decreased anxietyb.Decreased depressionc.Decreased level of dependence on medication.2.Participants in the neurofeedback mindfulness group will have significantly lower scores in migraine disability and intensity, and significantly higher scores in headache management self-efficacy when compared to the attention control group and the waitlisted group.3.Participants in the neurofeedback mindfulness group will have lower anxiety and lower depression scores when compared to the attention control group and the waitlisted group.4.Neurofeedback mindfulness participants will have a significant decrease in the level of dependence on medication, compared to those in the controlled intervention and waitlisted groups.5.There will be no impact of participants' belief in meditation on any of the measured criteria (e.g., migraine characteristics and psychiatric symptoms) across time.

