### The instruments

3.11

In this study, six measurements are given to participants at three time points during the study: before the intervention (Week 1), during the intervention (Week 4) and after completing the intervention (Week 8). On average, the total amount of time to complete six questionnaires is estimated around 13 min. These measurements (described in detail below) collect information about migraine disability (MIDAS), headache intensity (HIT-6), headache management self-efficacy (HMSE), anxiety (BAI), depression (CES-D), and severity of dependence on medications (SDS).1Migraine Disability Assessment Scale (MIDAS)

This 5-item instrument focuses on the number of headache-impacted missing days in the migraine population. MIDAS is shown to have significantly high internal consistency scores in United States (Cronbach's α = 0.76) and the UK (Cronbach's α = 0.73) [39].2Headache Impact Test-short form (HIT-6)

This 6-item scale collects information about the intensity of the headache attacks with high reliability of 0.90 Cronbach's ***α*** ([40]). This measurement is a short and sound psychometrical tool to assess how participants evaluate their headache severity.3.Headache Management Self-Efficacy Scale (HMSE)

This measurement is a 25-item scale that measures individuals' perceived level of coping and headache-related disability management with an excellent internal consistency (Cronbach's α = 0.90) [41]. The HMSE score predicts headache-related disability, as shown in MIDAS, regardless of the headache intensity, as usually shown in HIT-6 [41].4BECK Anxiety Inventory (BAI)

This 21-item instrument is a self-report of physical and cognitive symptoms of anxiety on and is validated with a moderate correlation with the revised Hamilton Anxiety Rating Scale (*r* = 0.51)([42]). Internal consistency of this measure is significantly high (Cronbach's α = 0.92) and test-retest reliability in a 1-week period was also acceptable (Cronbach's α = 0.75) [42].5.The Center for Epidemiologic Studies Depression (CES-D)

This validated 20-item scale is a short self-report of the original version with 300 items [43]. The internal consistency of this instrument is high (Cronbach's α = 0.85–0.90) and test re-test reliability is also acceptable (0.45–0.70) [39].6.Severity of Dependence Scale (SDS)

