### Statistical methods

3.12

This protocol is primarily based on comparing the baseline information of the participants with their information on Weeks 4 & 8 of their intervention. With regards to this, we will use Repeated Measures ANOVA for comparing the effect of time on the participants' changes in chronic headache characteristics, psychiatric symptoms, and medicine intake. Additionally, we will compare the interaction effect of time* groups to discover which of the three groups would show most significant changes across time as measured independently for each of the study's scales.

For each of the task-based groups, we will explore the total missed days and attrition at each of the task groups to discover the level of adherence for the two task-based groups. The diaries will also be compared across time to discover how participants manage their headaches via different alternatives and whether there is a change in their trend of headache medicine intake.

Finally, the EEG data analysis will be applied for within-subject and between subject comparisons to determine whether there is a change in adults with chronic migraine's peak alpha frequency over time and during their headache experiences as a function of their practices.

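### Six unranked scales each get their own time-by-group test, and the protocol does not say which result establishes efficacy, so the false-claim risk could be about 5–6% or as much as 11–26%

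*Protocol article*

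**What the plan says.** The main goal in section 2 (Hypotheses) is whether the intervention "could moderate headache experience (including frequency and intensity), headache management self-efficacy, psychiatric symptoms" and reliance on analgesics. Hypotheses 2 to 4 then compare the mindfulness group with both control groups. Hypothesis 2 covers disability, intensity and self-efficacy; hypothesis 3 covers anxiety and depression; hypothesis 4 covers medication dependence. Together they span all six scales, without a ranking.

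Section 3.11 (The instruments) lists MIDAS, HIT-6, HMSE, BAI, CES-D and SDS side by side: "six measurements are given to participants at three time points during the study".

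Section 3.9 (Participants) gives the sample size: "a sample size of 66 is expected to detect significance level of 0.05", with "95 % power through our planned statistical analysis test". The effect of time is examined "for each of the six measurements independently", and for the group comparison "we will compare the interaction of time*groups separately for each of our six scales". Section 3.12 (Statistical methods) looks for the group with the "most significant changes across time as measured independently for each of the study's scales".

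**The concern.** Efficacy in this design rests on the time-by-group interaction, and there are six of them with equal standing. With no primary scale and no stated decision rule, a reader of the results cannot tell whether one significant scale out of six confirms the treatment, or whether a whole hypothesis must succeed. Under the first reading, the chance of a false positive somewhere in the set is several times 0.05. The power statement has the same gap: it names one test and one significance level, but not the scale it belongs to.

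The choice matters more than usual here. Participants know their group (section 3.8, Blinding), and all six measures are questionnaires they complete themselves. Emphasis on whichever scale happens to succeed would therefore be easy and hard to detect.

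**Working it through.** **Inputs from the protocol.** Six scales, one interaction test each (3.9, 3.12); significance level 0.05, power 95%, N = 66, "our planned statistical analysis test, i.e., Repeated Measures ANOVA" (3.9); three groups at 1:1:1 (3.6); three time points (3.11); 180 allocated with up to 50% attrition (3.9, 3.10), so 180 × 0.5 = 90 completers.

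**Assumed, because not stated.** Between-scale correlation r from 0 to 0.9; correlation between repeated measures ρ = 0.5; effect size f as given below.

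**The plan's own figure.** The 66 cannot be reproduced from the stated inputs alone, because the article gives neither effect size nor correlation. It is matched under some assumptions, for example f = 0.25, ρ = 0.5, three groups and two measurements, interaction test (power 95.3%). With three measurements and the same f and ρ, the interaction needs 54. So 66 neither supports nor contradicts the point.

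**Reading A: any one significant interaction counts.** No true effect on any scale, each test at 0.05.
- Independent scales: 1 − 0.95^6 = 26.5%.
- Equally correlated two-sided normal statistics: 1 − ∫ p(x)^6 φ(x) dx, where p(x) = Φ((1.96 − √r·x)/√(1−r)) − Φ((−1.96 − √r·x)/√(1−r)).
- Check: simulation of six correlated time-by-group F tests, 3 groups of 22, three time points, 10,000 runs.

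**Reading B: hypotheses as joint claims.** A claim under hypothesis 2 needs all three of its scales, hypothesis 3 both of its scales, and hypothesis 4 its single scale. With q = 1 − p(x), the chance of at least one false claim is 1 − ∫ (1 − q³)(1 − q²)(1 − q) φ(x) dx. For independent scales this is 1 − (1 − 0.05³)(1 − 0.05²)(1 − 0.05) = 1 − 0.999875 × 0.9975 × 0.95 = 5.2%.

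| r | A, normal model | A, simulated F tests | B, normal model |
|---|---|---|---|
| 0 | 26.5% | 25.5% | 5.2% |
| 0.3 | 24.1% | 25.1% | 5.5% |
| 0.5 | 20.7% | 21.2% | 5.7% |
| 0.7 | 16.4% | 17.2% | 6.0% |
| 0.9 | 10.8% | 11.8% | 5.9% |

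Reading B leaves out the further demand in hypotheses 2 to 4 that both control groups be beaten.

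**Power if all six stay co-equal under Holm.** First-step level: 0.05/6 = 0.0083. Noncentral F for the interaction, λ = f²·N·3/(1 − ρ). Back-solving so that 66 gives 95% at 0.05, with three groups, three time points and ρ = 0.5, gives f ≈ 0.221.
- N = 66: λ = 0.221² × 66 × 3/0.5 = 19.3, df 4 and 126. Power is 95% at 0.05 and 83% at 0.0083.
- N = 90: λ = 0.221² × 90 × 3/0.5 = 26.4, df 4 and 174. Power is 95% at 0.0083.

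**The case against.** The strongest objection is that much of this is silence. Only an article is at hand. Running one ANOVA per scale does not say that the p-values go unadjusted, and Holm over six separate ANOVAs would fit the wording. The 0.05 appears only in the sample-size sentence. This stands in part: the article does not show that no adjustment will be made, and a reader who infers that goes beyond the text. What it does not answer is the ranking of outcomes. Which scale decides, and which scale the power figure refers to, is core protocol content. Sections 3.9 and 3.12 do address the matter, and they give all six scales equal standing.

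The second objection is that the hypotheses already supply a rule. They are grouped by construct and joined by conjunctions, and on that reading the error is close to 5%. This is fair, and it is why the 11–26% cannot be given as the trial's error rate. But the analysis sections judge each scale alone and never say that a hypothesis needs all its scales.

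Two stronger readings are tempting. A reader might add the six time-effect tests and arrive at a much larger error rate. Those tests pool the three groups, and change over time can occur without any treatment effect, so they do not test efficacy against control. A reader might also infer that adjustment would leave the trial underpowered, from the 83% at N = 66. That overlooks the roughly 90 completers the plan itself expects.

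**Conclusion.** The point holds in a limited form: the protocol tests six unranked scales separately and does not say which result establishes efficacy. The chance of at least one false efficacy claim is about 11–26% if each interaction is tested at 0.05 and any one suffices, and about 5–6% if hypotheses 2 and 3 are joint claims. Both figures assume no effect on any scale, and the between-scale correlations are assumed. Even at a correlation of 0.9, the any-one reading gives more than double 0.05. The defect is that the document leaves the choice between the two readings open, when it should be settled before the data are seen.

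**What to change.** In 3.9 and 3.12, name one of the six scales as primary, keep its planned three-group time-by-group test at 0.05, and state that the 66 participants and 95% power refer to that test. Treat the other five as secondary, tested with Holm. If the investigators prefer six co-equal scales, apply Holm across the six interaction tests instead, and say that each scale is then a separate claim.

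The cost is a short change of wording and stricter thresholds for the scales under Holm. With a single primary scale, the stated level, power and sample size for that test are unchanged. With six co-equal scales, first-step power is about 83% with 66 analysed and about 95% with 90, under the back-solved effect, so the 180 to be allocated need not change.

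The fix does not require replacing the three-group test with a Week 8 comparison of mindfulness against attention control. That would set aside the waitlist comparison in hypotheses 2 to 4 and need a new sample-size calculation.

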**Fig. 3 fig3:**
[figure not shown]
The flowchart for Participant Recruitment.

### Attrition

3.10

Due to the high demanding nature of chronic migraine and concerns with balancing expectations and time commitment for adults with chronic migraines, a high rate of attrition is expected. Previous non-migraine related RCTs have had attrition rates as high as 48 % [38]. With regards to previous similar studies on long-term use of neurofeedback in migraine populations with 75 % of attrition [22], we will speculate a high rate of attrition (50 %) for 8 weeks of joint neurofeedback mindfulness interventions.

### The instruments

3.11

In this study, six measurements are given to participants at three time points during the study: before the intervention (Week 1), during the intervention (Week 4) and after completing the intervention (Week 8). On average, the total amount of time to complete six questionnaires is estimated around 13 min. These measurements (described in detail below) collect information about migraine disability (MIDAS), headache intensity (HIT-6), headache management self-efficacy (HMSE), anxiety (BAI), depression (CES-D), and severity of dependence on medications (SDS).1Migraine Disability Assessment Scale (MIDAS)

This 5-item instrument focuses on the number of headache-impacted missing days in the migraine population. MIDAS is shown to have significantly high internal consistency scores in United States (Cronbach's α = 0.76) and the UK (Cronbach's α = 0.73) [39].2Headache Impact Test-short form (HIT-6)

This 6-item scale collects information about the intensity of the headache attacks with high reliability of 0.90 Cronbach's ***α*** ([40]). This measurement is a short and sound psychometrical tool to assess how participants evaluate their headache severity.3.Headache Management Self-Efficacy Scale (HMSE)

This measurement is a 25-item scale that measures individuals' perceived level of coping and headache-related disability management with an excellent internal consistency (Cronbach's α = 0.90) [41]. The HMSE score predicts headache-related disability, as shown in MIDAS, regardless of the headache intensity, as usually shown in HIT-6 [41].4BECK Anxiety Inventory (BAI)

This 21-item instrument is a self-report of physical and cognitive symptoms of anxiety on and is validated with a moderate correlation with the revised Hamilton Anxiety Rating Scale (*r* = 0.51)([42]). Internal consistency of this measure is significantly high (Cronbach's α = 0.92) and test-retest reliability in a 1-week period was also acceptable (Cronbach's α = 0.75) [42].5.The Center for Epidemiologic Studies Depression (CES-D)

This validated 20-item scale is a short self-report of the original version with 300 items [43]. The internal consistency of this instrument is high (Cronbach's α = 0.85–0.90) and test re-test reliability is also acceptable (0.45–0.70) [39].6.Severity of Dependence Scale (SDS)

This scale includes 5 questions that originally evaluate participants' level of dependence on different substances [37,44]. It has recently been validated to be effective with assessing dependence-like behaviours in subjects with MOH [45] with a high internal reliability (α = 0.72). This scale will be a reliable tool to assess participants’ changes in tolerance and need for increased amount of the medication to manage their headaches.

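### The migraine intensity hypotheses rest only on HIT-6, an instrument named for headache impact, and no dedicated intensity rating is tied to them

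*Protocol article*

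**What the plan says.** Section 2 (Hypotheses) gives the main goal as an effect on "headache experience (including frequency and intensity", among other outcomes. Hypothesis 1b predicts that intensity falls over time. Hypothesis 2 makes the between-group claim: "Participants in the neurofeedback mindfulness group will have significantly lower scores in migraine disability and intensity", together with higher self-efficacy, against both control groups.

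Section 3.11 (The instruments) lists six scales given at Weeks 1, 4 and 8 and pairs each with a construct. The intensity entry reads "headache intensity (HIT-6". The scale's own paragraph carries its full name, Headache Impact Test (short form), and then says: "This 6-item scale collects information about the intensity of the headache attacks". That paragraph adds that the tool serves to "assess how participants evaluate their headache severity". The paragraph on the self-efficacy scale repeats the label, saying that self-efficacy predicts disability "regardless of the headache intensity, as usually shown in HIT-6".

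Sections 3.9 (Participants) and 3.12 (Statistical methods) plan a repeated measures ANOVA for time and for time by group, run separately on each scale. Section 3.12 also says that the diaries will be compared over time for how participants manage their headaches and for trends in headache medicine intake.

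**The concern.** The name of the instrument and the construct assigned to it do not agree. Impact is what a headache does to the person. Intensity is how strong the headache is. The two can move together, but a treatment may shift one without the other.

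This matters more here than in most headache trials because of the article's own rationale. The Introduction (section 1) reports that a sham practice with focused attention may raise pain threshold about as much as mindfulness does, while mindfulness has the larger effect on how pain is observed and how unpleasant it is judged to be. It then sets up the attention control to learn whether a mindfulness routine is needed or whether simple attentional adjustment is enough. A treatment expected to work through appraisal and coping is one for which impact could improve with intensity unchanged. A conclusion of lower migraine intensity would then be wrong on a question that the trial was set up to answer.

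The Introduction also criticises other non-drug treatments for lacking evidence on pain severity or intensity, and calls for approaches that reduce both frequency and intensity. The intensity claim is therefore part of the stated case for the trial.

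**Working it through.** No arithmetic applies. The check traces the intensity hypotheses to the data that would test them.

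**Step 1. Which outcomes concern intensity?** Hypothesis 1 has six components: disability, intensity, self-efficacy, anxiety, depression and medication dependence. One of the six is intensity. Hypothesis 2 has three outcomes: disability, intensity and self-efficacy. One of the three is intensity. Hypotheses 3 and 4 concern anxiety, depression and dependence. Hypothesis 5 covers all measured criteria and so only inherits the label.

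**Step 2. What is each scale said to measure (section 3.11)?**

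| Scale | Construct as described | Named as an intensity measure? |
|---|---|---|
| MIDAS | "This 5-item instrument focuses on the number of headache-impacted missing days in the migraine population" | No |
| HIT-6 | Named an impact test; described as intensity and as perceived severity | Yes, by label only |
| HMSE | "perceived level of coping and headache-related disability management" | No |
| BAI | Anxiety symptoms | No |
| CES-D | Depression | No |
| SDS | Dependence on medication | No |

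HIT-6 is the only scale assigned to intensity, and no scale is named as a dedicated intensity rating.

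**Step 3. Is the label a slip?** No. HIT-6 is called a measure of intensity in the list of scales, in its own paragraph and in the HMSE paragraph. The mapping is consistent and deliberate, so it would carry through to the report.

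**Step 4. Which test decides the intensity hypotheses?** Sections 3.9 and 3.12 analyse each scale independently. The time effect on HIT-6 is therefore the test of 1b, and the time-by-group effect on HIT-6 is the test of the intensity part of hypothesis 2.

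**Step 5. Could the diaries supply intensity?** Section 3.5 (Intervention follow up) describes 24 multiple-choice questions on recent headaches, in the paragraph about the waitlisted group. The items are not listed. Section 3.12 uses the diaries for headache management and medicine intake. No intensity endpoint is drawn from them, and nothing links them to 1b or 2.

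**Result.** As written, a HIT-6 change becomes a statement about migraine intensity, with no separate intensity measure to confirm or contradict it.

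**The case against.** The strongest reply is that every descriptive sentence about HIT-6 calls it a measure of intensity or severity, and only its name says impact. The items are not reproduced and the cited validation sources are not at hand. This reply stands in part. A reader might infer that none of the six scales captures intensity at all. The documents do not support that, because some HIT-6 items may touch on severity. What remains is that no dedicated intensity rating is named and that the only scale used for intensity is named for something else.

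A reader might also infer that HIT-6 duplicates MIDAS, so that 1a and 1b test the same thing. No section says so. Section 3.11 describes MIDAS as counting missed days and sets it apart from HIT-6. The overlap is a guess from the names and is not relied on here.

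A third tempting step is to put a loss of power on the mismatch. That would need a correlation between impact and intensity and a true intensity effect, and the article gives neither. A simple two-group comparison at Week 8 would also not be the planned repeated measures ANOVA. No such figure is justified.

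Two further replies have some weight. The unseen diary may contain an intensity item, and leaving out its items is ordinary condensation in an article. But the analysis the article does state takes no intensity endpoint from the diary. It is also true that the HIT-6 data and test are the same under either label, and that the instrument is named openly. What changes is the conclusion drawn from that test, and the hypotheses fix that conclusion as intensity.

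**Conclusion.** The concern holds in a limited form. Hypothesis 1b and the intensity part of hypothesis 2 depend solely on an instrument that the article itself names an impact test. A positive HIT-6 result would support a statement about headache impact. It would not by itself support the planned statement about migraine intensity.

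The size is one of six components of hypothesis 1 and one of three outcomes in hypothesis 2. A reader might take this as undermining two of the five hypotheses as a whole. It does not, because the other components of hypotheses 1 and 2 have their own scales, and hypotheses 3 and 4 are untouched. Sample size and error rates are not affected, and the HIT-6 data stay usable.

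The conclusion rests on two things: the name of the instrument as printed in section 3.11, and the premise, drawn from the Introduction, that mindfulness may act on appraisal and coping apart from intensity. How often impact and intensity would diverge in this population cannot be judged from the document.

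**What to change.** 1. In hypotheses 1b and 2 and in section 3.11, state the HIT-6 outcome as *headache impact*.
2. Test intensity with one 0-10 item on average headache intensity, added to the Week 1, 4 and 8 questionnaires in all three arms, and name it as the outcome for the intensity hypotheses. An existing diary intensity item would serve instead, if there is one and all arms complete it.
3. If no item can be added, for example because data collection has begun, keep the rewording and draw no intensity conclusion from HIT-6.

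The cost is one extra question on a set estimated at about 13 minutes, and a seventh outcome beside six that are already tested separately. The rewording alone costs nothing in data collection and removes the misattribution.
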